## Abstract

**Background:**

Cancer-related fatigue (CRF) is a commonly experienced and often debilitating side effect of cancer treatment that can persist for years after treatment completion. The benefits of cognitive behaviour therapy (CBT) for CRF are well established; however, these interventions are typically not included in standard clinical care. Traditional CBT is resource-intensive, limiting implementation in hospital settings. Stepped-care approaches can offer benefits to more people, using the same personnel as traditional models.

**Method/design:**

This is a single-arm feasibility study. Fifty people with a cancer diagnosis, at least 12 weeks post-treatment or on long-term maintenance treatment, with persistent CRF that is affecting daily activities, will enrol in a stepped-care CBT program. Intervention: The stepped-care program involves two steps. Step 1: All participants begin with a 5-week supported self-management CBT progam targeting fatigue. Step 2: If fatigue remains severe or has changed less than the minimal clinically important difference on the fatigue measure after step 1, participants will be offered four sessions of therapist-directed group CBT. Measures: Participants will complete questionnaires at baseline and 6 and 10 weeks. The primary outcome is feasibility of the REFRESH program. The implementation evaluation comprises acceptability, satisfaction, appropriateness, and feasibility of the study intervention, along with administrative data including cost, processes, procedures and implementation. Secondary outcomes are changes in fatigue, quality of life and self-efficacy.

**Conclusion:**

The REFRESH program will be the first stepped-care CBT intervention for persistent CRF in Australia. Assessing feasibility of REFRESH is an important first step to establishing future implementation and efficacy.

## Background

Cancer-related fatigue (CRF) refers to the distressing and persistent subjective sense of physical, emotional and/or cognitive exhaustion related to cancer and/or cancer treatment [1]. Further, CRF is not proportional to recent activity and is not alleviated with sleep or rest [2] Approximately half of people receiving cancer treatment report moderate to severe CRF, and it can be debilitating years after treatment completion for up to one in three survivors [3]. Fatigue significantly interferes with everyday tasks, employment, physical and social activities. It further inhibits functional recovery and treatment adherence, with additional adverse impact on functional cognition (e.g. attention and concentration) and emotional wellbeing, including increased depression symptoms and lower quality of life [4, 5]. Whilst there is some evidence that fatigue has little impact on task performance in advanced cancer [6], the distressing nature and consequences of fatigue symptoms can be significant for many months or years following cancer treatment [7, 8].

Medications for CRF are not recommended except to relieve suffering in advanced disease [9] and non-pharmacologic interventions are therefore recommended to treat CRF [10]. Cognitive behaviour therapy (CBT) is an evidence based psychological treatment used for a range of psychological symptoms [11] and is the internationally recommended first line of treatment for persistent CRF [10]. The goal of CBT is to change unhelpful ways of thinking and modify learned patterns of unhelpful behaviour to reduce unpleasant emotions and physical distress.

The causal assumption for effectiveness of CBT for CRF relates to addressing the psychological and lifestyle factors that maintain fatigue [12, 13]. Physical inactivity or over-activity, worry and rumination, mood disturbance, sleep problems, pain, inadequate nutrition and low self-efficacy have all been identified as maintaining factors for CRF [10, 14]. These maintaining factors of CRF are bi-directional and create a vicious cycle for individuals. Cognitive and behavioural factors associated with increased fatigue and poorer functioning include all-or-nothing thinking, catastrophizing and avoidance behaviour [15]. The goal of CBT for persistent CRF is to target unhelpful behaviours, thoughts and emotions associated with CRF maintaining factors in order to reduce fatigue severity and fatigue-related disability [16].

The effectiveness of CBT for CRF has been established in a small number of studies across the Netherlands, Germany and UK [12, 16, 17]. In a recent systematic review of the effectiveness of psychological interventions for fatigue in cancer survivors, 12 of the 33 randomised controlled trials reported on the effects of CBT on CRF [18]. Five of these 12 studies compared CBT with treatment as usual, all reporting a significant decline over time in fatigue for the intervention group. The remaining seven studies in this review combined CBT with, or compared CBT to, another intervention, typically physical activity [18]. Whilst these results are promising, the CBT programs varied considerably in content and delivery, and only two targeted fatigue. Several programs included a high treatment dose of up to 26 face-to-face or online sessions with a psychologist, and others utilised web-based methods.

Resource-intensive programs for CRF are simply not feasible and sustainable, where healthcare manpower or expertise are limited. Additionally, a program must have demand, be acceptable, affordable, accessible and show promise for efficacy in order to be feasible longer term [19] The feasibility of embedding a CBT program for fatigue into “real world” clinical settings (outside of the research context) that considers these program priorities has not been established in Australian cancer services.

One approach to enhancing feasibility of CBT for CRF, particularly in a resource restricted environment, is to use a stepped-care intervention that can cater for individuals with differing needs. An example of stepped-care is to provide low-intensity treatments (e.g. self-help resources) as a starting point, with a ‘stepped up’ pathway to specialist services as clinically required. Whilst therapist-directed CBT is gold standard delivery, self-directed CBT is also effective [20, 21], and therefore utilising a stepped-care model of CBT can potentially benefit more patients with the same personnel as traditional delivery.

This paper describes a research protocol to investigate the feasibility of stepped-care CBT for individuals experiencing persistent CRF, entitled ‘REFRESH’ (ACTRN: ACTRN12622000420741). This is a single-arm exploratory study design. Standard Protocol Items: Recommendations for Interventional Trials (SPIRIT) guidelines were used to guide the reporting of the current feasibility study (see Fig. 1). The primary aim of the REFRESH study is to examine the acceptability, satisfaction, appropriateness and feasibility of an evidence-informed stepped-care CBT intervention for adults with persistent fatigue after cancer treatment. A secondary aim is to explore whether participation in the stepped-care intervention shows promise for improvements in fatigue, quality of life and self-efficacy.

**Fig. 1 Fig1:**
[figure not shown]
SPIRIT: overview of REFRESH. Superscript digit one (1) indicates the following: the Functional Assessment of Chronic Illness Therapy—Fatigue; superscript digit two (2) indicates the following: Perceived Self Efficacy for Fatigue Self-Management; superscript digit three (3) indicates the following: European Quality of Life 5 Dimension 5 Level; superscript digit four (4) indicates the following: Acceptability of Intervention Measure; superscript digit five (5) indicates the following: Intervention Appropriateness Measure; superscript digit six (6) indicates the following: Feasibility of Intervention Measure; superscript digit seven (7) indicates the following: Client Satisfaction Questionnaire; superscript digit eight (8) indicates the following: perceived improvements to personal, social and lifestyle factors (self-devised); superscript digit nine (9) indicates the following: perceived satisfaction with step 2 (self-devised). Asterisk (*) indicates the following: these measures will only be completed in the t2 questionnaire by those who have completed STEP 1 and STEP 2 of the intervention

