As a contingency, participants who are too distressed or unable to engage with the self-help program within two weeks after commencing STEP 1 can be fast tracked to STEP 2 (see below).

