#### Time 1 assessments (T1)

After 5 weeks, participants will complete a follow-up questionnaire. The T1 questionnaire includes fatigue, quality of life and self-efficacy questions (repeated T0 measures), in addition to feasibility and satisfaction measures (see “study measures” below).

#### Eligibility for STEP 2

Eligibility for STEP 2 is based on a participant’s change in fatigue scores following STEP 1. Fatigue will be measured using the Functional Assessment of Chronic Illness Therapy—fatigue subscale (FACIT-F) scores [22]. Participants with a T1 FACIT-F score greater than 34 or at least 10 points greater than T0 will be encouraged to continue their strategies without further CBT intervention. Participants with a FACIT-F score on the T1 questionnaire below 34 (severe) or less than 10 points greater than T0 will be considered for STEP 2 in conjunction with a psychologist’s clinical judgement of further support needs.

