#### Time 2 assessments (T2)

At 10 weeks post T0 (for STEP 1 only completers) or at the completion of STEP 2, all participants will complete a final T2 questionnaire. Completion of the T2 questionnaire marks the end of participation in the REFRESH study.

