### Data analysis

The target sample of 50 participants is based on available funding, resources (e.g. clinician time to deliver STEP 2) and study duration of 12 months. Whilst this sample size is in line with pilot and feasibility trials reported elsewhere [32], there is yet to be a clear consensus as to appropriate sample size for feasibility studies [33].

Analyses will include all available data and will be performed in R (reference index version 3.6.1 or higher) [34]. Descriptive statistics will be used to summarise demographic and clinical characteristics of all study participants. These will include counts and percentages for nominal and crude-scale ordinal (< 10 levels) valued variables and means and standard deviations or medians and interquartile ranges, as appropriate, for fine-scale (≥10 levels) ordinal and continuous valued variables.

The main implementation outcomes are acceptability, satisfaction, appropriateness and intervention feasibility of the stepped-care CBT intervention. These will be summarised using descriptive statistics. Recruitment data will be summarised using a rate and 95% CI using the Poisson distribution. Adherence and retention data will be summarised using a proportion and 95% CI; this will be estimated using the Wilson method.

Changes from baseline at follow-up assessments for fatigue (FACIT-F), self-efficacy (PSEFSM) and quality of life (Ed-5D-5L) will be analysed descriptively (means and standard deviations). This will be done separately for participants who undertake STEP 1 only and for those who participate in STEP 1 and STEP 2. Effect size estimates (i.e. standardised measures of change from baseline; in this case, mean change divided by the baseline standard deviation), as described by Kazis, Anderson and Meenen [35] will be used to characterise the size of observed differences.

Free text items from participant questionnaires will be summarised using content analysis, whereby the content of free responses will be coded and grouped, where applicable. Since the free text items mostly accompany pre-determined response options, it is not envisaged that all participants will respond to free-text items.

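### Read literally, the Fig. 1 legend collects the asterisked T2 ratings only from people who completed both steps, omitting STEP 2 dropouts and fast-tracked participants

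*Protocol article*

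**What the plan says.** The Fig. 1 legend lists nine measures, among them acceptability, appropriateness, feasibility, client satisfaction and "perceived satisfaction with step 2 (self-devised"). It then adds the asterisk rule: "these measures will only be completed in the t2 questionnaire by those who have completed STEP 1 and STEP 2 of the intervention". Which measures carry the asterisk is shown only in the figure, which is not available here.

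Four other places bear on that rule.

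- **STEP 1 section.** There is a route into STEP 2 that bypasses the rest of STEP 1: "participants who are too distressed or unable to engage with the self-help program within two weeks after commencing STEP 1 can be fast tracked".
- **Time 1 assessments (T1).** The T1 questionnaire repeats the baseline measures "in addition to feasibility and satisfaction measures".
- **Time 2 assessments (T2).** T2 falls 10 weeks after T0 for those who have STEP 1 only, "or at the completion of STEP 2, all participants will complete a final T2 questionnaire".
- **Data analysis.** "The main implementation outcomes are acceptability, satisfaction, appropriateness and intervention feasibility of the stepped-care CBT intervention". These are summarised descriptively from whatever data are available. Change scores are shown separately for people who had STEP 1 only and people who took part in both steps.

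The Background gives these outcomes the same standing: "The primary aim of the REFRESH study is to examine the acceptability, satisfaction, appropriateness and feasibility".

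**The concern.** The asterisk rule decides who is asked, not how answers are analysed. A rating that was never requested cannot be recovered later by an analysis plan or by a policy of using all available data. If the rule is applied as written, the group rating STEP 2 is selected on having got through the whole program. The omitted people are informative about whether stepped care suits its users: those who left STEP 2, and those for whom the self-help step did not work and who went straight to a therapist. Acceptability, satisfaction, appropriateness and feasibility are the primary aim, so completer-only selection in the post-STEP 2 ratings touches what the study is meant to report.

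**Working it through.** There is no planned figure to reproduce. The sample of 50 rests on funding, resources and duration, and no completion rate or rating is assumed anywhere. The check is therefore a reading of the sections against each other, followed by an illustration of direction and size.

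**Step 1: apply the legend to each route.**

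| Route | Meets the legend's condition, read literally? | T2 time stated? |
|---|---|---|
| STEP 1 only | No (never had STEP 2) | Yes, 10 weeks after T0 |
| STEP 1 completed, STEP 2 completed | Yes | Yes, at completion of STEP 2 |
| STEP 1 completed, STEP 2 started and stopped | No | No |
| Fast-tracked, STEP 2 completed | No (STEP 1 not completed) | Yes, at completion of STEP 2 |
| Fast-tracked, STEP 2 started and stopped | No | No |

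The first exclusion is sensible. The last three concern people who received some or all of STEP 2 and are not asked. Two of those three also have no stated T2 time, although the T2 section covers all participants.

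**Step 2: see whether other data fill the gap.** On the standard route the T1 measures are taken before STEP 2 begins, so they cannot rate it. Table 2 plans withdrawal records, session attendance, reasons for missed sessions and the share completing STEP 2. These show that people stopped, and partly why. They are not ratings, and they say little about a fast-tracked person who attends every session.

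**Step 3: direction and size (all inputs assumed).** Let f be the share of STEP 2 starters left out, Rc the completers' value and Re the value among those left out. The value for all starters is (1 − f)·Rc + f·Re, so

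completer-only value minus all-starter value = f × (Rc − Re).

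The sign depends on whether those left out are less or more satisfied than completers. With 25 starters and about 85% of completers satisfied:

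| Completers satisfied | Left out | Of those left out, satisfied | All starters | Difference (points) |
|---|---|---|---|---|
| 19/22 = 86.4% | 3 | 0, 1 or 3 | 76%, 80% or 88% | +10.4, +6.4 or −1.6 |
| 17/20 = 85% | 5 | 0, 2 or 5 | 68%, 76% or 88% | +17, +9 or −3 |
| 13/15 = 86.7% | 10 | 0, 4 or 10 | 52%, 68% or 92% | +34.7, +18.7 or −5.3 |

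For example, with 5 left out and 2 of them satisfied: (17 + 2)/25 = 76%, and 0.20 × (0.85 − 0.40) = 0.09.

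The scales are more likely to be reported as scores than as a percentage satisfied. On an average item score coded 1 to 5 (coding assumed), with f from 0.1 to 0.4, the completer mean is too high by 0.05 to 0.20 if those left out score 0.5 lower, and by 0.10 to 0.40 if they score 1.0 lower. It is unchanged if they score the same, and too low by 0.05 to 0.20 if they score 0.5 higher.

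**The case against.** The strongest reply is that this is loose wording. The asterisk may simply keep people who had STEP 1 only from being asked about a STEP 2 they never received. The Data analysis section separates the same two groups by participation, and the T2 section uses completer language as a label for a pathway. Completion of STEP 1 is not defined, and people who miss a chapter are encouraged to carry on. All of this is fair. If participation was meant, though, the legend states a stricter condition than intended, and even participation in both steps leaves a fast-tracked person's status unclear.

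A reader might infer more than the document supports, in four ways.

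- **That the acceptability, appropriateness, feasibility and client satisfaction scales are all restricted at T2.** The plural in the legend suggests more than one item, but without the figure nothing ties the asterisk to those four. Nor are the main outcomes as a whole conditional on completion, because feasibility and satisfaction measures are also taken at T1 without that limit.
- **That the ratings are certainly biased upward.** This is plausible for people who left STEP 2. Fast-tracked participants struggled with a booklet and may rate therapist-led sessions higher or lower.
- **That a poorly accepted STEP 2 would pass unnoticed.** Heavy dropout would show in the withdrawal, attendance and completion data, and adherence and retention are reported with confidence intervals.
- **That nothing would be learned about fast-tracking.** Fatigue, self-efficacy and quality of life at T2 are planned for all participants, and the asterisk is not shown to remove them.

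The study is also exploratory, with descriptive summaries and no success threshold on these ratings, so no formal decision turns on them.

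**Conclusion.** The point stands in a limited form. As written, the legend confines the asterisked T2 measures to people who completed both steps. It fits poorly with the fast-track route, with T2 for all participants, and with the participation-based grouping in the analysis. If the rule is followed literally, ratings of STEP 2 after it has been delivered will be missing for dropouts and fast-tracked participants, and no planned data replace them. At the least this affects satisfaction with STEP 2, the one listed measure specific to that step.

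The missing ratings follow directly from the literal rule; the bias does not. Overstatement is probable where dropouts are less satisfied, the direction is open for fast-tracked participants, and the size cannot be derived from the document. The assumed scenarios run from about 35 points too high to about 5 points too low, which shows only that the effect could matter when STEP 2 numbers are small. The change is worth making because it is nearly free and the ratings serve the primary aim.

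**What to change.** 1. Replace the asterisk rule in the Fig. 1 legend so that the marked measures go to all participants who attended at least one STEP 2 session, whether or not they completed STEP 1 or STEP 2.
2. In the T2 section, state when T2 is given to participants who stop STEP 2 early.
3. Report each of these measures with the number rated beside the number who started STEP 2, so that non-response is visible. For mean or median scores, the number who started is given alongside and is not used as a divisor.
4. Align the Fig. 1 legend, the fast-track provision in the STEP 1 section, the T2 section and the grouping in Data analysis, and say in which group fast-tracked participants are counted.

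The cost is questionnaire branching, a few sentences of text and a few more items for a small number of participants. Scores may come out lower. The fast-track route and the offer of STEP 2 are unchanged.

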## Methods

### Participants

Fifty adults with a cancer diagnosis who have completed treatment at Peter MacCallum Cancer Centre in Melbourne, Australia, at least 12 weeks prior to study enrolment, or are on long-term maintenance treatment, who have moderate to severe CRF will be recruited to REFRESH.

### Participant inclusion criteria

Each participant must meet the following criteria to participate in the study:Aged 18 years or older at the time of recruitment, able to speak and read EnglishReports moderate to severe persistent fatigue based on study screening questionsCompleted primary treatment for any cancer at least 3 months priorOR has been on long term maintenance treatment (e.g. single agent immunotherapy or targeted therapy) for melanoma or a blood cancer for at least 3 months with partial or complete tumour responseOR is diagnosed with a chronic blood cancer but below treatment threshold (no active treatment or ‘watch and wait’)

### Participant exclusion criteria

Participants will be excluded from the study if the clinical screening interview identifies:A likely significant sleep disorder and/orCurrent psychosis, significant psychological distress or risk of self-harmFatigue is not *persistent* (i.e. duration less than 4 weeks)

### Participant recruitment and consent

Participants will be recruited from outpatient specialist clinics at Peter MacCallum Cancer Centre. Tumour stream nurses, medical or allied health professionals will identify patients, during routine clinical care, who are reporting fatigue symptoms. Additional recruitment measures will include promotional postcards in waiting areas, study advertisements in newsletters, emails to medical and allied health staff and presentations at staff meetings. The health professional will then notify the research team. A researcher will telephone the patient to discuss the study and, if the person indicates interest, will screen for eligibility. The eligibility screen includes a series of questions based on Canadian guidelines for assessing CRF [10]. The eligibility screening questions are (1) a self-report score of 4 or more to the question “On a 0 to 10 scale where 0 means no fatigue and 10 means the worst fatigue imaginable, how would you rate your fatigue at its worst over the past 3 days?”; (2) moderate to severe symptoms of fatigue assessed using qualitative descriptors adapted from Canadian fatigue guideline [10] by endorsing any item indicating moderate to severe fatigue (e.g. “fatigue is noticeable and upsetting” (moderate fatigue) or “exercise does not seem possible” (severe fatigue); and (3) endorsing ‘yes’ to the question “Has fatigue been affecting your day to day life for one month or more?”.

Those meeting full eligibility criteria will be offered follow up care in the REFRESH study. People with mild fatigue, who are not eligible for the research study, and individuals who are eligible but decline participation will be directed to online CRF resources to prevent exacerbation of fatigue symptoms.

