**Feasibility of materials and CBT group attendance**	The extent to which stepped care approach to CBT can be used for cancer fatigue	A majority of participants complete step 1 in 6 weeks and/or step 2 in 4 sessions	**□ The Feasibility of Intervention Measure (FIM)**^a^ **□** Open-ended study-devised questionnaire items (e.g. number of chapters of the self-management booklet attempted/completed)
**Cost**	The resource cost of delivering the program per user	This self-help CBT program is expected to provide therapy at a lower cost compared to face to face, enabling more users to benefit	**□** Booklet cost and records of therapist/administration time per person enrolled **□** Proportion of participants requiring step 2
**Fidelity**	The degree to which the program was implemented as intended [24]	The adherence and deviations to program contacts and stepped care protocol	**□** Field notes maintained by researchers **□** Session checklist after each STEP 2 session to ensure all topics covered

^a^The AIM, IAM and FIM are 4-item (each) validated measures with items rated on a 5-point Likert scale from ’completely disagree’ to ‘completely agree’ with higher scores indicating greater intervention acceptability, appropriateness and feasibility respectively [25]

^b^The CSQ [26] is a well validated 8-item measure of the quality of the intervention, the extent to which the program met participant’s needs, perceived increases in skills and whether participants would recommend the program to others. Total scores range from 8 to 56, with higher scores indicating greater satisfaction

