#### FACIT-Fatigue (Functional Assessment of Chronic Illness Therapy—Fatigue subscale)

The FACIT-F is a valid measure of the severity of cancer-related fatigue, with a recall period of 7 days [22]. FACIT-F is a 13-item scale, with items rated on a 5-point Likert scale from 0 (not at all) to 4 (very much). Score range is 0–52, with the population mean of 43 [27]. Lower scores on the FACIT-F indicate greater fatigue and impairment. A FACIT-F score below 34 is considered to be severe [28] and a 10-point improvement a clinically important difference [29].

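### Entry admits moderate fatigue with no FACIT-F limit, but routing after STEP 1 uses FACIT-F 34 and a 10-point gain, so STEP 2 need and improvement depend partly on the baseline score

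*Protocol article*

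**What the plan says.** **Entry.** The Participants section states the target group as people "who have moderate to severe CRF will be recruited to REFRESH". Participant recruitment and consent lists three screening requirements: "a self-report score of 4 or more to the question" about worst fatigue over three days on a 0–10 scale; "endorsing any item indicating moderate to severe fatigue"; and a yes to "Has fatigue been affecting your day to day life for one month or more". FACIT-F is first completed in the T0 questionnaire, after consent. No FACIT-F value is required for entry, and everyone then starts STEP 1.

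**Routing.** Eligibility for STEP 2 has two sentences. The exit sentence reads: "Participants with a T1 FACIT-F score greater than 34 or at least 10 points greater than T0 will be encouraged to continue their strategies". The STEP 2 sentence covers a T1 score under 34 or a gain of fewer than 10 points; such participants are considered for STEP 2 together with a psychologist's judgement. The abstract words the rule as "If fatigue remains severe or has changed less than the minimal clinically important difference on the fatigue measure after step 1".

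**Meaning of the thresholds.** The FACIT-Fatigue section says: "A FACIT-F score below 34 is considered to be severe [28] and a 10-point improvement a clinically important difference". It gives a range of 0–52, with lower scores meaning worse fatigue, and a population mean of 43.

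**Use of the results.** Table 2 lists "Proportion of participants requiring step 2" under Cost. The Discussion ties the programme's potential reach to at least half of participants improving meaningfully on STEP 1 alone.

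**The concern.** Entry and routing use different instruments with different severity targets. The screen deliberately lets in moderate fatigue, whereas the routing level of 34 marks severe fatigue, and the abstract's wording that fatigue *remains* severe presupposes a severe start that entry does not require.

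Two consequences follow. A person who starts above 34 satisfies the level part of the exit sentence before opening the booklet, so leaving by that route says nothing about whether STEP 1 helped. A person who starts close to the top of the scale has no room to show the 10-point change.

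At stake is the reading of two figures: the share needing STEP 2, which drives therapist time, and the share improving on STEP 1 alone. Both can move with who happens to enrol, even if STEP 1 has the same effect on everyone.

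**Working it through.** There is no power-based figure to reproduce: the sample of 50 rests on funding, resources and duration. The check is scale arithmetic, a full listing of score pairs, and a sensitivity range.

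**1. Scale limits.** 13 items × 4 points = 52. The highest T0 that allows a 10-point gain is 52 − 10 = 42, so T0 of 43–52 cannot show it. T0 of 35–52 already exceeds 34.

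**2. Routing of every integer pair (T0, T1).** There are 53 × 53 = 2809 pairs. Exit means T1 > 34 or T1 − T0 ≥ 10. STEP 2 means T1 < 34 or T1 − T0 < 10.

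| Sentences met | Pairs |
|---|---|
| Exit only | 646 |
| STEP 2 only | 1530 |
| Both | 633 |
| Neither | 0 |

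The 633 split into two groups:
- T1 > 34 with a gain under 10: sum of (62 − T1) for T1 = 35 to 52, which is 27 + 26 + … + 10 = 333.
- T1 < 34 with a gain of 10 or more: sum of (T1 − 9) for T1 = 10 to 33, which is 1 + 2 + … + 24 = 300.

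Of the 333, those with T0 of 35 or more number (10 + 11 + … + 18) + 9 × 18 = 126 + 162 = 288. Every unchanged participant with T0 of 35 or more is among them. These are counts of possible pairs, not probabilities.

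**3. Examples.**
- 42 to 35 is a 7-point worsening. It meets the exit sentence (35 > 34) and the STEP 2 sentence (gain under 10).
- 44 to 52 ends at the best possible score. The gain is 8, so it too meets both sentences.

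**4. How many people? (assumed)** No baseline FACIT-F is given and nothing maps the 0–10 rating to FACIT-F. I take T0 as normal with mean m and SD s, truncated to 0–52 with continuity correction:

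P(T0 > 34) = [Φ((52.5 − m)/s) − Φ((34.5 − m)/s)] / [Φ((52.5 − m)/s) − Φ((−0.5 − m)/s)], with 42.5 in place of 34.5 for T0 > 42.

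| Mean, SD (assumed) | T0 > 34: share, of 50 | T0 > 42: share, of 50 |
|---|---|---|
| 22, 8 | 0.059, 3.0 | 0.005, 0.3 |
| 25, 10 | 0.169, 8.5 | 0.037, 1.9 |
| 30, 10 | 0.318, 15.9 | 0.095, 4.7 |
| 34, 10 | 0.463, 23.1 | 0.171, 8.6 |
| 36, 8 | 0.566, 28.3 | 0.192, 9.6 |
| 36, 12 | 0.509, 25.4 | 0.229, 11.5 |

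**5. Effect on the two figures.**
- *STEP 2 need if nobody changes.* If the exit sentence prevails, the share of STEP 2 candidates is 1 − P(T0 > 34): 68% at mean 30 and SD 10, and 94% down to 43% across the range. If the STEP 2 sentence prevails, it is 100%.
- *10-point improvement.* Reaching 25 of 50 requires that share from the people able to gain 10. At mean 30 and SD 10 this is 25/(50 − 4.7) = 55% of them. Across the range it runs from 25/(50 − 0.3) = 50% to 25/(50 − 11.5) = 65%.

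**The case against.** The case against has several sound parts.

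- **Frequency is not shown.** A reader might infer that some entrants will certainly start above 34 and some can never improve by 10. The documents do not support that as fact. A start above 34 is likely, because moderate is not severe. A start at 43 or more means scoring at or above the quoted population mean while passing all three screening requirements. That is possible, but its frequency is unknown.
- **Starting above 34 does not settle the route.** A reader might infer that such people simply count as needing no STEP 2. The STEP 2 sentence also captures anyone who gains under 10 points, and psychologist judgement follows. The text gives two answers, not one.
- **The two routing harms are alternatives.** If either condition permits exit, the ceiling keeps nobody from exiting. If both are required, nobody exits unchanged, but T0 of 43 or more can never exit by score. For routing, therefore, the fault is tied to the contradiction between the two sentences. The ceiling on the improvement proportion remains under either reading.
- **The 10 points are a change criterion.** Only 34 is a severity cut-off.
- **The figures carry limited weight.** The STEP 2 proportion is one of the Cost measures, beside booklet cost and staff time, and as a resource measure it properly reflects case mix. The at-least-half remark sits in the Discussion, where the article concedes the study lacks power for effectiveness. Data analysis plans mean changes and effect sizes, not a responder analysis.

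What stands is that clinical judgement decides who receives STEP 2 but does not separate people who improved from people who were already above 34.

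**Conclusion.** The point holds as an inconsistency between the entry criteria and the routing thresholds. By arithmetic alone, any entrant at 35–52 meets the exit sentence without improving and, with a gain under 10, meets the STEP 2 sentence too. Any entrant at 43 or more cannot meet the 10-point criterion. Contradictory routing is not confined to these people: someone who gains 10 points but stays below 34 also meets both sentences.

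The size is uncertain. On the assumed distributions, about 3 to 28 of 50 start above 34 (about 16 at mean 30, SD 10) and about 0.3 to 11.5 at 43 or more (about 5). I read the Discussion's meaningful improvement as the 10-point difference in the FACIT-Fatigue section, since no other definition is given.

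The STEP 2 proportion is not invalid as a measure of resource use. What the plan cannot support is reading it, or exit by level, as evidence that STEP 1 worked. The remedy is nearly free, so it is worth making before analysis.

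**What to change.** 1. Reconcile the abstract, Participant recruitment and consent, Eligibility for STEP 2 and FACIT-Fatigue so that each T0/T1 pair leads to one route. Which clinical cut-off and which combination of conditions apply is for the investigators.
2. Keep the overall STEP 2 proportion as a resource measure. Beside it, report STEP 2 need and 10-point improvement by T0 FACIT-F: 34 or below, 35–42, and 43 or more.
3. Do not count exit by the 34 level as STEP 1 improvement when T0 was already above 34, and state that the 10-point criterion is unattainable at T0 of 43 or more.

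Do not rest the STEP 1 claim on low-T0 participants alone without saying so plainly: in a single-arm study, selecting low baseline scores brings in regression to the mean.

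The cost is wording and a few table rows, as T0 FACIT-F is already collected. The bands will be small. With the Wilson method the article already uses for adherence and retention, an observed proportion of one half has 95% half-width 1.96 / (2√(n + 1.96²)). That gives 37% to 63% for 25 of 50, 34% to 66% for 17 of 34, and 28% to 72% for 8 of 16. A top band of about 5 people would be descriptive only.
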